### Interim analyses {21b}

No interim analyses are planned.

### Methods for additional analyses (e.g., subgroup analyses) {20b}

At present, no subgroup analyses are planned.

### Methods in analysis to handle protocol non-adherence and any statistical methods to handle missing data {20c}

With the randomization and intervention taking place in the operating room, we expect no protocol non-adherence. Prior to surgery, we will ensure that all preoperative questionnaires are completed, which should reduce the risk of missing baseline data. We will handle missing primary outcome data using multiple imputation by chained equations (MICE) under a missing-at-random assumption. The imputation model will include treatment group and pre-specified prognostic variables (including baseline characteristics and any available intermediate/follow-up measurements) to generate m imputed datasets; each dataset will be analyzed using the planned regression model for the dichotomous outcome (e.g., logistic regression), and estimates will be combined using Rubin’s rules.

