### Outcomes {12}

#### Primary outcome measure

Difference between the groups in the rate of participants with radiologically verified recurrence at 1 year after surgery. Recurrence is defined as any part of the stomach or other abdominal viscera located above the diaphragm at computed tomography (CT).

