#### Secondary outcome measures

Between group differences in the following:
Rate of radiologically verified recurrence at 3 years.Mean GSRS (gastrointestinal symptoms rating scale) component scores of reflux, abdominal pain, indigestion, diarrhea, and constipation at 3 months, 1 year, and 3 years postoperatively.Mean Short-Form 36 (SF-36) physical and mental component scores at 3 months, 1 year, and 3 years postoperatively.Mean Dakkak dysphagia scores at 3 months, 1 year, and 3 years postoperatively.Frequency of reflux disease-related symptoms (heartburn, reflux, chest pain, dysphagia of liquids and/or solids, odynophagia, globus sensation, respiratory symptoms, nightly cough, and odynophagia categorized on a four-level scale at 3 months, 1 year, and 3 years postoperatively).Rates and severity of complications at 30 days postoperatively. Complications will be classified according to Clavien-Dindo [34].Mean postoperative length of stay in days.Size and type of recurrence. Size will be measured in cm above the diaphragm. Type will be classified as types I–IV.

These metrics were chosen to assess both the objective and subjective effectiveness of the intervention as well as the safety. There is currently no core outcome set available that defines standardized outcome indicators for paraesophageal hernia repair, although it is in development [35]. The GSRS, SF-36, and Dakkak questionnaires are all validated instruments [36–38]. The reflux disease-related frequency questionnaire has been used in numerous previous studies from the same institution. Taken together, these instruments enable a comprehensive coverage of symptoms related to paraesophageal hernias.

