### Sample size {14}

Previous studies have suggested recurrence rates after paraesophageal hernia repair ranging from 7 to 66% [15–20]. We have estimated the recurrence rate to be 30% in the control group and hypothesize that this can be reduced to 10% with the addition of gastropexy. With an α of 0.05 and a power of 80% (β = 0.2), we calculate a required sample size of 62 participants per arm, yielding a total of 124 evaluable participants. To account for an estimated 15% loss to follow-up, based upon previous studies with similar follow-up at the same institution, we aim to include 150 participants. The primary analysis will use multiple imputation under a missing-at-random assumption to include all randomized participants; this approach is expected to preserve the planned power under the anticipated missingness.$$\begin{aligned}n&=\left[\sqrt{\frac{\left(0.3+0.1\right)}{2}\left(1-\frac{\left(0.3+0.1\right)}{2}\right)\left(1+\frac{1}{1}\right)}\ 1.96\ \right.\\&\left.+\ \sqrt{0.3\left(1-0.3\right)+\frac{0.1\left(1-0.1\right)}{1}}0.84\right]^{2}/{0.2}^{2}\approx 62\end{aligned}$$

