## Data collection and management

### Plans for assessment and collection of outcomes {18a}

Participants will undergo a study-specific low-dose CT scan of the upper abdomen and lower thoracic cavity at 1 and 3 years, with a permissible variation of ± 3 months from the specified time points. The CT protocol can be found in Supplement A. If a participant undergoes a clinically indicated CT scan that includes the upper abdomen and lower thoracic cavity within the specified time frame, the study-specific CT scan may be omitted. The CT scans will be reviewed by a specialized radiologist, blinded to the participants’ group allocation, to assess for recurrence.

Postoperative data including length of stay, complications, and reoperations will be collected by a research nurse or research fellow 30 days postoperatively. Severity of complications is graded according to the Clavien Dindo classification [34].

Patient-reported outcome measures (PROMs), including quality of life and the severity and frequency of symptoms, will be assessed at baseline, 3 months, 1 year, and 3 years. Health-related quality of life will be assessed with the Swedish version of the Short Form-36 (SF-36) questionnaire (RAND Corporation). SF-36 consists of 36 items grouped in eight domains, which can be summarized to mental and physical component scores [39–42].

The Gastrointestinal symptom rating scale (GSRS) measures symptoms of reflux, abdominal pain, indigestion, diarrhea, and constipation. The questionnaire consists of 15 items and uses a 7-point Likert scale, with 1 representing no symptoms and 7 representing severe symptoms. Scores are summarized for each of the five domains [38, 39].

The Dakkak dysphagia score assesses dysphagia. Participants report frequency (never, sometimes, or always) of dysphagia when eating nine types of solid, mashed, and liquid food. The generated score ranges from 0 to 45, where we will reverse the original scoring as done in previous studies, so that a higher score indicates more severe dysphagia [36, 37].

Additionally, a specific questionnaire will be used to assess the frequency of specific symptoms of heartburn, reflux, chest pain, dysphagia, globus sensation, respiratory symptoms, nightly cough, odynophagia as well as difficulty vomiting or belching.

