## Statistical methods

### Statistical methods for primary and secondary outcomes {20a}

Analyses will be performed on an intention-to-treat basis. Descriptive statistics will be used to present overall and group-wise data.

The primary outcome will be analyzed using logistic regression with treatment group as the main independent variable, with pre-specified co-variates including age, BMI, and hiatal area.

Secondary categorical outcomes will be analyzed using logistic regression and continuous outcomes using linear regression. Continuous outcomes with repeated measurement will be analyzed using linear mixed-effect models.

Exploratory post hoc analyses will assess the association between surgeon experience, defined as the number of prior paraesophageal hernia repairs performed, and primary and secondary outcomes.

All analyses will be performed using R Statistical Software (version 4.4.1, 2024–06–14, R Core Team, Vienna, Austria).

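### The planned multiple imputation does not reach 3-year recurrence: a default logistic fit would omit participants without a 3-year CT, losing precision and possibly shifting the rates

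*Protocol article*

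**What the plan says.** Section {20c} of the protocol article sets out the missing-data method: "We will handle missing primary outcome data using multiple imputation by chained equations (MICE) under a missing-at-random assumption". The Sample size section {14} gives it the same scope: "The primary analysis will use multiple imputation under a missing-at-random assumption to include all randomized participants". The imputation model contains treatment group and prognostic variables, "including baseline characteristics and any available intermediate/follow-up measurements", and results are pooled with Rubin's rules.

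The first item under Secondary outcome measures is "Rate of radiologically verified recurrence at 3 years". It is also listed first among the secondary objectives in {7}. For its analysis, {20a} states: "Secondary categorical outcomes will be analyzed using logistic regression and continuous outcomes using linear regression". Mixed-effects models are reserved for continuous outcomes measured repeatedly, so they do not apply to a binary CT result. The same section says "Analyses will be performed on an intention-to-treat basis", without limiting this to the primary outcome.

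On collection, {18a} states: "Participants will undergo a study-specific low-dose CT scan of the upper abdomen and lower thoracic cavity at 1 and 3 years". A clinically indicated CT inside the window may replace the study scan. No section says what happens in the 3-year analysis when the scan is missing.

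**The concern.** Two of the three kinds of follow-up outcome have a route for partly observed participants: imputation for 1-year recurrence, and a likelihood-based mixed model for the repeated questionnaire scores. Three-year recurrence has neither. Logistic regression in R, the stated software, drops rows with a missing response by default.

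The information lost is not trivial. The 1-year CT result is likely to be the best available predictor of 3-year status, and it will already be in the database. If attendance at 3 years depends on that result, data are missing at random only after conditioning on it. A complete-case model with arm and baseline covariates does not do that. At stake is the trial's only CT evidence on durability beyond 1 year.

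**Working it through.** **The plan's own figure.** With 30% v 10%, n = [√(0.2 × 0.8 × 2) × 1.96 + √(0.21 + 0.09) × 0.84]² / 0.2² = [1.109 + 0.460]² / 0.04 = 61.5, so 62 per arm as stated. Then 124 / 0.85 = 145.9, which 150 covers. This concerns the 1-year outcome. The article gives no power, recurrence rate or missingness for 3 years.

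**Inputs.**
- From {14}: 75 per arm (150 at 1:1), and 1-year recurrence of 30% v 10%.
- Assumed: 3-year recurrence of 45% v 20%; every 1-year recurrence still present at 3 years; the missed-scan proportions below.

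Under these assumptions the control arm splits into 0.30 recurred by year 1, 0.15 new by year 3 and 0.55 never. The intervention arm splits into 0.10, 0.10 and 0.80. The full-data difference is 25 points, with odds ratio (0.20/0.80) / (0.45/0.55) = 0.306.

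**Complete-case rate** = [r₁(1 − m₁) + new × (1 − m₀)] / [r₁(1 − m₁) + (1 − r₁)(1 − m₀)], where m₁ and m₀ are the proportions missing the 3-year CT with and without a 1-year recurrence.

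*40% / 15%, both arms (20% missing overall).*
- Control: (0.18 + 0.1275) / (0.18 + 0.595) = 0.3075 / 0.775 = 39.7%.
- Intervention: (0.06 + 0.085) / (0.06 + 0.765) = 0.145 / 0.825 = 17.6%.
- Difference 22.1 points; odds ratio (0.145/0.68) / (0.3075/0.4675) = 0.324.
- Known recurrences omitted: 75 × 0.30 × 0.40 = 9 control, 75 × 0.10 × 0.40 = 3 intervention.

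*50% / 20%, both arms (26% missing overall).*
- Control 0.27 / 0.71 = 38.0%; intervention 0.13 / 0.77 = 16.9%.
- Difference 21.1 points; odds ratio 0.331.

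*40% among 1-year recurrences in one arm only, 15% for everyone else.*
- Control arm affected: 39.7% v 20%, difference 19.7 points, odds ratio 0.25 / 0.658 = 0.38.
- Intervention arm affected: 45% v 17.6%, difference 27.4 points, odds ratio 0.213 / 0.818 = 0.26.

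*25% / 25%, both arms.* Rates stay at 45% v 20%, so there is no bias. About 56 per arm are analysed.

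**Power** (1,500 simulated trials, 20 imputations using the 1-year CT, z above 1.96):

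| Missing with / without 1-year recurrence | Complete case | Imputed |
|---|---|---|
| 25% / 25% | 84.1% | 86.5% |
| 40% / 15% | 77.3% | 89.1% |
| 50% / 20% | 72.5% | 88.5% |

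A separate unadjusted simulation (3,000 trials) gave 81% v 86%, 75% v 87% and 70% v 87%: the same pattern. The assumption that recurrences persist favours imputation, because it makes a positive 1-year CT a perfect predictor.

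**Sensitivity to the assumed rates.** Take no new recurrences after year 1 and 50% / 15% missing in both arms. The difference shrinks from 20 to 14 points, and the odds ratio stays at 0.26. With 10% of the others recurring later in each arm, the difference goes from 18 to 13 points and the odds ratio from 0.40 to 0.47.

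**The case against.** The strongest reply is that this reads a rule into silence. No sentence restricts the 3-year analysis to those scanned, bars imputation for secondary outcomes, or excludes a participant with a known 1-year recurrence. The article is a condensed account, {31c} refers to a full protocol that is not shown, and missing-data rules for secondary outcomes often sit there or in an analysis plan. This stands. A reader might infer that the plan drops known recurrences and so contradicts its own intention-to-treat statement. The documents do not support that: the dropping follows from the default behaviour of the named model, and the general intention-to-treat sentence points, if anything, the other way.

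The second reply is about size. The planned model estimates an odds ratio, and with equal dependence in both arms that moves from 0.306 to 0.324 or 0.331, which is 5% to 7% on the log scale. This also stands, so a flat statement that the comparison is biased goes too far. It does not dispose of the point, because the outcomes section defines the measure as a between-group difference in rates, and both the rates and their difference do shrink.

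The third reply is that the only loss figure is 15%, and nothing in the article shows that people with a recurrence attend less. They could be scanned more often, since clinically indicated CTs count. That is right, and it leaves the direction of any bias open. The loss of precision remains whatever the direction.

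**Conclusion.** The point holds as a cheap improvement, not as an error. As written, imputation covers the primary outcome only, and the method named for 3-year recurrence makes no use of the 1-year CT and by default omits participants without a 3-year scan.

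The firm part is lost precision: about 84% v 87% power at 25% missing unrelated to the 1-year result, under the assumed rates. The conditional part is bias. There is none if attendance is unrelated to the 1-year result. With 40% / 15% missing in both arms, the difference is about 3 points too small and the odds ratio barely changes. If the dependence differs by arm, the odds ratio ranges from 0.26 to 0.38 against 0.31. All of this rests on assumed 3-year rates, persistence of recurrence and assumed attendance. The documents supply none of these, so the figures show what could happen, not what is expected.

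**What to change.** Add a sentence to {20c} extending the planned MICE procedure to 3-year recurrence. Predictors: treatment arm, the pre-specified baseline covariates, the 1-year CT result (recurrence and size) and the follow-up questionnaire scores. Fit the same covariate-adjusted logistic model as for the primary outcome, pool with Rubin's rules, and report complete-case analysis as a sensitivity analysis.

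The sentence should also settle how a known 1-year recurrence without a 3-year CT is counted. Simply counting it as a recurrence while dropping other unscanned participants is not neutral. With 30% v 10% true, no new recurrences and 15% missed scans, it gives 0.30 / 0.895 = 33.5% v 0.10 / 0.865 = 11.6%.

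Cost: one sentence and a little more analysis work with a procedure already planned. No new data are needed, and recruitment is still open. The downside is reliance on missing-at-random given the 1-year result, which the complete-case analysis will not fully test.

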### Plans to give access to the full protocol, participant level data, and statistical code {31c}

No public access will be granted to the full protocol, participant-level data, or statistical code.

## Oversight and monitoring

### Composition of the coordinating center and trial steering committee {5d}

The study will be coordinated by a research team at Ersta hospital including the principal investigator, surgeons, research fellows, and research nurses. The steering committee consists of the research team as well as surgeons from major participating sites. The steering committee is planned to have regular meetings approximately four times annually to monitor the progress of the study and to consider input from the data monitoring committee and safety committee.

### Composition of the data monitoring committee, its role and reporting structure {21a}

The trial has an independent data monitoring committee (DMC) consisting of three members. The DMC will monitor all data related to study participant inclusion, informed consent, and primary outcome. In addition, the DMC will monitor random samples from every fifth to tenth study participant to ensure adherence to protocol regarding the accuracy and completeness of case report forms, questionnaires, and the randomization process. The DMC will meet at least twice yearly and report findings to the trial steering committee. The full monitoring plan can be found in Supplement B.

### Adverse event reporting and harms {22}

All severe adverse events (SAE), defined as Clavien Dindo ≥ 3b, will be reported to a safety committee (SC) consisting of two independent members, both experienced senior surgeons. Data regarding SAEs provided to the SC by the study coordinator will be partially blinded, allowing treatment arms to be differentiated as group A and B, but allocation to the control arm or intervention arm will remain unknown to the SC. The SC may give recommendations on protocol alterations to the trial steering committee. The SAE report form can be found in Supplement C.

### Frequency and plans for auditing trial conduct {23}

The trial steering committee will evaluate trial conduct at scheduled meetings four times a year.

### Plans for communicating important protocol amendments to relevant parties (e.g., trial participants, ethical committees) {25}

Significant protocol amendments will be communicated without delay to all investigators as well as the national ethical review authority. Amendments that affect participants, including changes to follow up or data management, will be communicated to affected participants.

### Dissemination plans {31a}

The results of the trial will be published in a peer-reviewed medical journal targeting healthcare professionals and planned to be included in a doctoral thesis. All participants will be informed at the end of the study period whether they were allocated to the control or intervention arm.

## Discussion

Current guidelines usually recommend surgical treatment for patients with symptomatic PEH, but the optimal technical approach remains debated [7, 43–46]. Despite decades of experience with PEH repair, recurrence rates remain high, with reported rates even exceeding 50% [19].

The impact of tension created during hernia repair for recurrence rates is well documented in other types of hernia repair, including inguinal and ventral hernias [47]. It has been proposed that tension in PEH repair originates from two directions: axial tension related to repeated esophageal shortening and lateral tension caused by narrowing of the separated hiatal crura during the operation. In attempts to reduce tension and counteract the transdiaphragmatic pressure gradient promoting recurrence, various adjunct techniques have been evaluated.

Mesh reinforcement has been used with the aim to reduce the tensile forces at the crural suture line (mainly addressing the lateral tension). However, studies on the use of mesh adjacent to the esophagus in laparoscopic PEH repair have yielded conflicting results, with worrisome reports of severe mesh-related complications [48, 49]. Additionally, recent meta-analyses have shown similar long-term recurrence rates with or without mesh reinforcements, questioning its routine use [50–52]. An alternative to mesh reinforcement is to reduce the crural tension by adding a diaphragmatic relaxing incision. While retrospective studies have shown promising results, this has not been properly evaluated until quite recently [53]. Based on the lack of evidence behind the efficacy of mesh reinforcement, irrespective of the type of mesh used, the traditional crural repair should still be considered “standard of care,” especially when exploring other approaches to minimize the recurrence risk after PEH repair.

For addressing axial tension, procedures for esophageal lengthening such as wedge-fundectomy and traditional Collis gastroplasty have been proposed [2, 43, 54]. None of these techniques has so far been evaluated in a randomized clinical trial assessing recurrence following PEH repair. In clinical practice, several strategies to counteract axial forces have been employed, including various attempts to “anchor” the stomach and the reconstruction within the abdominal cavity. Placement of a gastrostomy tube has also been used to provide fixation of the anterior aspect of the stomach to the abdominal wall. Hernia reduction with gastropexy alone was described in the original studies from the early 1950 s [23, 55–57] but thereafter mostly abandoned, except as an alternative approach in high-risk patients [2]. While smaller series have reported promising results, up until quite recently, the use of gastropexy as an adjunct to a PEH repair in uncomplicated cases where the stomach and distal esophagus can be replaced to the abdomen without excessive tension has not been evaluated in a scientifically rigorous manner [2, 37, 58, 59]. However, in a recent randomized study, it was shown that an anterior gastropexy with two transfascial sutures significantly reduced the 1-year recurrence rate in patients undergoing PEH repair [60]. Notably, the majority of patients in this study did not receive an antireflux procedure, which is regarded as the established standard of care in PEH repair, supported by current evidence and recommended in clinical guidelines [9, 12, 13, 61]. Albeit this important study supports the relevance of gastropexy to reduce the risk of recurrence, a study is warranted to address the effect of gastropexy when added to a standard of care PEH repair.

In the current study protocol, we compare extensive gastropexy, with three fixation points, to no gastropexy at all in the control group. To minimize the risk of potential confounders due to technical differences, we have opted for a standardized PEH repair. While many surgeons may prefer at least some fixation of the stomach, evidence supporting the use of any type of gastropexy in PEH repair is only emerging. In addition, there are no data suggesting that several points for gastropexy reduce recurrence rates compared to fewer. We have therefore chosen to compare two “extremes”: gastropexy with a maximal fixation in the intervention group compared with no fixation at all in the control group. If our data show an advantage with the use of gastropexy, the optimal type of fixation needs to be addressed in future studies.

The primary endpoint in our study is radiologically verified recurrence at 1 year. Since many patients with recurrence of PEH after surgical repair report minor or no symptoms, it is important to assess whether observed differences between groups are clinically relevant [19]. To address this, our study incorporates PROMs evaluating both generic health-related quality of life and disease-specific symptoms. By combining objective and patient-reported outcomes, we aim to provide robust evidence to guide future clinical practice and improve long-term outcomes for patients undergoing PEH repair.

